### Study design

2.4

This study is a non-randomised, uncontrolled, non-interventional, prospective imaging study.

This study will enrol patients with radiological diagnosis of grade IV glioma and for whom a diagnosis of glioblastoma, IDH wild type is confirmed on neuropathological exam, according to the WHO 2021 glioma classification criteria (33). Patients fulfilling the inclusion criteria will receive standard of care treatment according to the Stupp protocol (34), with the addition of OE and BOLD MRI and [^18^F]MISO PET scans to routine diagnostic protocols (**Figure 2**). MRI scans employing OE and BOLD sequences, as well as [^18^F]MISO PET/CT scans, will be acquired for patients pre-operatively at diagnosis, prior to commencement of chemoradiation treatment (3-4 weeks post-operative) and 12 weeks following completion of radiotherapy. Supplementary OE and BOLD MRI scans will also be performed in a test/retest setting prior to commencement of radiotherapy as well as during radiotherapy if the patients are amenable. If there is suspected recurrence on long term MRI surveillance, patients will be invited for repeat OE/BOLD MRI and [^18^F]MISO PET/CT scans. [^18^F]MISO PET imaging will be used to establish ground truth presence of hypoxia in the tumour. Existing correlations between MRI-derived levels of hypoxia and hypoxia levels assessed via [^18^F]MISO PET uptake will be evaluated (35–39). This study will require recruitment of a sample of 20 patients, as in previous clinical trials (NCT03716986, NCT02466828 and NCT00906893).

**Figure 2 f2:**
[figure not shown]
Diagram of study interventions flowchart.

### Study setting

2.5

In total, two sites will be utilised on the Northern Sydney Local Health District, Sydney, NSW, Australia: Royal North Shore Hospital (RNSH) and North Shore Radiology (NSR). Patients presenting with radiological symptoms of high-grade glioma at either of these sites will be presented with the opportunity to enrol in this study. This study is expected to recruit 20 patients. Following initial recruitment, NSR will be the site at which all the MRI scans will be performed, while RNSH will be the site at which the PET scans will be performed. Consent procedures may be performed at either site.

### Selection of subjects

2.6

#### Inclusion criteria

2.6.1

Male and female patients aged 18 years or older with suspected high-grade glioma at initial radiological examination and confirmed neuropathological diagnosis of glioblastoma, IDH wild type according to the WHO 2021 glioma classification criteria (33) will be recruited. Qualifying patients must have an Eastern Cooperative Oncology Group (ECOG) performance status score of 0-2, be available for scanning on two separate days and provide written informed consent for participation in this trial once eligibility is met.

#### Exclusion criteria

2.6.2

Women lactating, pregnant or of childbearing potential who are not willing to avoid pregnancy during the studyPatients with a history of severe renal disease(s) (eGFR<20) who cannot tolerate gadolinium chelate contrast agentsNeuropathological diagnosis not consistent with glioblastoma IDH wild typeGeographically remote patients unable to agree to imaging schedulePatients who have received anti-VEGF monoclonal antibody therapy within 3 months prior to recruitmentPatients with a history of psychological illness or condition such as to interfere with the patient’s ability to understand the requirements of the studyPatients with significant cardiac or pulmonary disease including cardiac arrythmias or Chronic Obstructive Pulmonary Disease (COPD) that are unable to tolerate high flow O_2_ for oxygen contrast.Patients taking carbonic anhydrase inhibitors (Acetzaolamide)History of glaucomaAny contraindication to MRI imaging.

### Interventional methods

2.7

#### MRI protocol

2.7.1

At each of the imaging timepoint determined in the study design patients will undergo the following MRI scans (**Figure 3**):

OE MRI: including T_1_ mapping sequence prior to oxygen challenge, T_1_-weighted dynamic sequence (40) during oxygen challenge, T_1_ mapping sequence during oxygen challenge;BOLD MRI: T_2_ mapping sequence, T_2_* mapping sequence, T_2_* dynamic sequence during oxygen switch off, DSC sequence with single bolus of gadolinium-based contrast agent.

**Figure 3 f3:**
[figure not shown]
Schematic of oxygen delivery protocol and MRI sequences acquisition.

MRI scans will be acquired on Siemens 3T systems (Vida) with a 64-channels head coil.

Details of the MRI sequences acquisition parameters are collected in **Table 1**. T_1_-weighted dynamic imaging will be performed with a golden-angle radial sparse parallel-volumetric interpolated breath-hold (GRASP-VIBE) that permits reconstruction of image volumes at retrospectively determined temporal resolution (40). The DSC MRI sequence will be acquired to characterize tissue perfusion, which will be important in the analysis of MRI/PET images to identify regions of the tumour where hypoxia is not induced by poor tissue perfusion (41).

**Table 1 T1:** MRI scan protocol acquisition parameters on a Siemens 3T scanner.

Parameter	T_1_ mapping + T13D (MP2RAGE)	T_1_w-dynamic (GRASP-VIBE)	T_2_ mapping (GRAPPATINI)	T_2_* mapping (MAPiT)	T_2_*w- dynamic (GRE-EPI)	DSC (GRE-EPI)
**Acquisition time**	3:30 min	6:45 min	2:07 min	3:47 min	4:18 min	1:26 min
**Resolution (mm^3^)**	1×1×1	1×1×1	0.7×0.7×4.0	1.7×1.7×4.0	1.7×1.7×4.0	1.7×1.7×4.0
**Matrix size**	240×256x192	256×256x104	320×240x30	128x128x30	128x128x20	128x128x20
**TR (ms)**	5000	4.51	5000	880	1230	1230
**TE (ms)**	2.9	1.65	16 TEs, TE1 = 10 ms, TE step=10 ms	12 TEs, TE1 = 6 ms, TE step=5 ms	30	30
**Flip angle**	0°	2°	180°	30°	90°	90°
**Number of averages**	1	1	1	1	1	1

During OE MRI acquisition patients will sequentially breathe medical air and 100% O_2_ (up to 15 l/min) through nasal prongs or oxygen mask. During DSC sequence acquisition, patients will be injected intravenously with a dose of 0.1 mmol/kg gadolinium-based contrast agent (GBCA) at a rate of 3-5 ml/s.

#### MRI analysis

2.7.2

Quantitative T_1_, T_2_ and T_2_
^*^ maps will be derived from in-line processing of the T_1_-mapping, T_2_-mapping and T_2_
^*^-mapping sequences, respectively, available on the scanner as part of the Siemens license agreement. Examples of quantitative images obtained from a healthy volunteer are shown in **Figure 4**. T_1_ maps for each timepoint of the T_1_-weighted dynamic acquisition will be calculated from static T_1_ maps by assuming that signal changes are due to T_1_ effects only, which is reasonable for sequences with very short echo times. These T_1_ maps calculations will be performed via an in-house software and a commercially available brain tumour imaging software, IB DCE (Imaging Biometrics LLC, Elm Grove, WI, USA). Cerebral blood flow (CBF) and cerebral blood volume (CBV) maps will be derived from kinetics modelling of the DSC data performed using the industry-leading brain tumour imaging software, IB Neuro (Imaging Biometrics LLC, Elm Grove, WI, USA).

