**Figure 4 f4:**
[figure not shown]
Example of quantitative images obtained from MRI protocol acquisition on a healthy volunteer.

A region of interest (ROI) will be delineated with a semi-automated tool and checked by an experienced neuroradiologist on the T_2_-weighted image as the hyperintense regions around the tumour. The ROI will be propagated to the T_1_, T_2_, T_2_
^*^ and CBF maps. Voxel-wise and median values of R_1_, R_2_, R_2_
^*^ and CBF within the ROI will be calculated from the quantitative T_1_, T_2_, T_2_
^*^ and CBF maps, respectively. The reproducibility, repeatability and accuracy of the quantitative-MRI protocol will also be assessed using guidelines and a phantom developed by the National Institute of Standards and Technology and the International Society of Magnetic Resonance in Medicine (42).

On one hand, HTV will be defined via OE MRI as the proportion of voxels within the ROI being refractory in R_1_ for O_2_ challenge [i.e. ▵R_1_ ≤ 0, where ▵R_1_ = R_1_ (O_2_) – R_1_ (air)] and well-perfused (i.e. CBF > 0), as previously determined by experts in the field (36, 41, 43, 44). ▵R_1_ will be calculated in two ways. First, it will be calculated from the R_1_ maps obtained from the T_1_-mapping sequences acquired before [R_1_ (air)] and during O_2_ breathing [R_1_ (O_2_)]. Second, it will be calculated from T_1_ maps derived from the T_1_-weighted dynamic acquisition, such that R_1_ (air) is derived from the average of the first two R_1_ maps acquired at baseline while breathing air and R_1_ (O_2_) is derived from the last four R_1_ map acquired during oxygen breathing. ▵R_1_ values obtained with the two approaches will be compared. The approach which will provide the most reliable ▵R_1_ values in the test-retest scan across the entire patient cohort will then be selected to calculate the HTV. Voxel-wise ΔR_1_ values in the HTV will be converted into values of partial pressure of oxygen (pO_2_) using a similar approach to the one used by Chakhoyan et al. (35), which exploits known values of pO_2_ in normal appearing white and gray matter and uses these values to calibrate the pO_2_ values in the tumour. This approach will provide a way to quantitatively measure voxel-wise levels of hypoxia.

On the other hand, HTV will be defined via BOLD MRI by using a previously established method to estimate relative oxygen extraction fraction (rOEF) in human gliomas from T_2_, T_2_

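### If the printed 2° flip angle is right, the dynamic ΔR1 magnifies non-T1 signal change about 5 to 8 times, and choosing the method on test-retest reliability alone would not reject a bias that repeats

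*Protocol article*

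**What the plan says.** Section 2.7.2 (MRI analysis) obtains a T1 map for each dynamic time point from the static T1 maps by "assuming that signal changes are due to T_1_ effects only, which is reasonable for sequences with very short echo times". No other justification is given.

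Table 1 in section 2.7.1 gives the acquisition. Its first two columns are MP2RAGE (static T1 mapping) and GRASP-VIBE (T1-weighted dynamic). The TR row begins "TR (ms) 5000 4.51" and the flip-angle row begins "Flip angle 0° 2° 180". The dynamic sequence is therefore printed with TR 4.51 ms and a flip angle of 2°; its TE is 1.65 ms.

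Section 2.7.2 then computes ΔR1 in two ways. One uses the static maps before and during oxygen. The other uses the dynamic series, where "R_1_ (air) is derived from the average of the first two R_1_ maps acquired at baseline while breathing air"; the oxygen value comes from the last four maps. A voxel joins the OE hypoxic tumour volume (HTV) if ΔR1 ≤ 0 and CBF > 0, and ΔR1 in the HTV is converted to pO2. The two sets of values are compared. The choice between them, which fixes the source of the HTV, is worded as follows: "The approach which will provide the most reliable ▵R_1_ values in the test-retest scan across the entire patient cohort will then be selected".

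**The concern.** The T1-only assumption needs two things: that little else changes the signal, and that the signal responds well to T1. The short-TE argument addresses only one part of the first, namely T2* decay. It does not cover drift, motion, inflow or proton-density change, and it says nothing about the second. A short-TR gradient echo at 2° is mainly proton-density weighted. When its signal is inverted to R1, any small change from another source is scaled up.

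Because the cut-off is zero, the sign of ΔR1 decides whether a voxel counts as hypoxic, so even a small systematic shift can move voxels across it. If the dynamic method is chosen, its ΔR1 defines the OE HTV, which enters the Dice and Pearson measures of the primary objective (section 2.3.1).

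**Working it through.** The plan states no figure on this point, so there is none to reproduce.

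**Inputs from the document:** TR 4.51 ms, TE 1.65 ms and flip angle α = 2° (Table 1); cut-off ΔR1 ≤ 0 (section 2.7.2). For scale, ΔR1 = 0.04 ± 0.04 s⁻¹ in the nasal concha of one healthy volunteer (Discussion).

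**Assumed inputs:** tissue T1 of 1.0, 1.5 and 2.0 s (the document gives none); ideally spoiled steady state without a preparation pulse (Table 1 lists none); a signal drift of 0.5%; an oxygen-induced R2* fall of 1 s⁻¹.

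**Model:** S = M0 · sin α · (1 − E)/(1 − E cos α) · exp(−TE · R2*), with E = exp(−TR · R1).

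**Sensitivity:** s = d ln S / d ln R1 ≈ (1 − cos α)/[(1 − cos α) + TR · R1]. A fractional non-T1 signal change is read as 1/s times that fraction in R1.

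At T1 = 1.5 s, 1 − cos 2° = 0.000609 and TR · R1 = 0.00451/1.5 = 0.003007. So s ≈ 0.000609/0.003616 = 0.168 (0.169 without the approximation), and 1/s ≈ 5.9.

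- Drift of +0.5%: to first order 0.005 × 5.93/1.5 = 0.0198 s⁻¹; numerical inversion gives 0.0203.
- R2* fall of 1 s⁻¹: the signal rises by exp(0.00165 × 1) − 1 = 0.17%. To first order 0.00165 × 5.93/1.5 = 0.0065 s⁻¹; inversion gives 0.0066.

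Results by inversion:

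| Assumed T1 | s at 2° | 1/s at 2° | 1/s at 8° (comparison only) | Signal change for ΔR1 0.04 s⁻¹, 2° | Apparent ΔR1, +0.5% signal, 2° | Apparent ΔR1, R2* fall 1 s⁻¹, 2° |
|---|---|---|---|---|---|---|
| 1.0 s | 0.119 | 8.4 | 1.46 | 0.46% | +0.044 s⁻¹ | +0.014 s⁻¹ |
| 1.5 s | 0.169 | 5.9 | 1.31 | 0.96% | +0.020 s⁻¹ | +0.007 s⁻¹ |
| 2.0 s | 0.213 | 4.7 | 1.23 | 1.60% | +0.012 s⁻¹ | +0.004 s⁻¹ |

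Over a wider assumed T1 range of 0.8 to 3.0 s the magnification at 2° runs from 10.2 to 3.5. The 8° column shows that the large factor comes from the printed 2°.

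**Direction.** An R2* fall raises the signal, so a voxel with unchanged R1 reads as ΔR1 > 0 and leaves the HTV. Drift can go either way: at T1 1.0 s a 0.5% fall reads as −0.0405 s⁻¹, enough to cancel a true +0.04 s⁻¹ and label a responding voxel refractory.

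**Selection rule.** Write the observed ΔR1 as true value + bias + random error. Test-retest reliability responds to the random error. A bias that is the same in both scans cancels in their difference, so the rule cannot see it.

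**The case against.** The strongest objection is to the premise. The same flip-angle row prints 0° for MP2RAGE, which could give no signal, and the document calls the dynamic sequence T1-weighted. A misprint is a real possibility; at 8°, for instance, the magnification would be only 1.2 to 1.5. This stands, and it makes the finding conditional.

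Second, the sizes are modest and rest on assumed inputs. At T1 1.5 s the R2* effect is about one sixth of 0.04 s⁻¹ (0.007/0.04) and the 0.5% drift about half of it (0.020/0.04). The 0.04 itself comes from one volunteer's nasal concha, not from brain or tumour. If that SD of 0.04 s⁻¹ is borrowed as voxel scatter, an R2* fall of 1 s⁻¹ moves the chance that a truly unchanged voxel has ΔR1 ≤ 0 from 50% to about 43%. This also stands.

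Third, the plan has safeguards: two methods, a comparison of their values, a reliability-based choice and a phantom assessment of accuracy. Low T1 sensitivity also magnifies noise, so the rule may well reject the dynamic method. That is fair for random error. It does not cover a repeating bias: the comparison does not enter the stated rule, and a phantom does not reproduce oxygen-related signal change in vivo.

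A reader might infer that the OE HTV will systematically miss refractory voxels and that agreement with PET will fall. The documents do not support this. Drift can have either sign, the R2* change is assumed, and no effect on HTV, Dice or Pearson has been computed. A reader might also infer that the flip angle should be changed. That would split a longitudinal cohort of 20 patients, and the concern can be met in the analysis alone.

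**Conclusion.** The point holds in conditional form. Short TE alone does not justify the T1-only assumption. On the printed parameters a fractional non-T1 signal change is magnified about 8.4 to 4.7 times into R1 for assumed T1 of 1.0 to 2.0 s. The resulting apparent ΔR1 values are not negligible against a cut-off of zero, and the selection rule as written would not reject such a bias if it repeats.

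This rests on an ideally spoiled steady state and on the assumed T1, drift and R2* values. It matters only if 2° is the flip angle actually used and the dynamic method is the one selected. The consequence for the primary endpoint is unquantified. It merits a change because the remedy is cheap and protects the OE HTV.

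**What to change.** 1. Verify the flip-angle row of Table 1 against the scanner protocol, covering both the 2° for GRASP-VIBE and the 0° for MP2RAGE, and correct it where needed.
2. If 2° is confirmed, state that the OE HTV is defined from the static T1-map ΔR1, and keep the dynamic ΔR1 exploratory.
3. If the true flip angle differs and the dynamic method remains a candidate, extend the selection rule in section 2.7.2. Before it can be chosen, the dynamic ΔR1 should show acceptable bias against the static T1-map ΔR1 as well as test-retest reliability. The limit should be set before agreement with PET is examined.

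The cost is one table check, a sentence or two of analysis wording and slightly more analysis. The static maps are already in the protocol, so acquisition and scan time do not change. The downside is the possible loss of the dynamic method as the primary source of ΔR1.

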**Figure 4 f4:**
[figure not shown]
Example of quantitative images obtained from MRI protocol acquisition on a healthy volunteer.

A region of interest (ROI) will be delineated with a semi-automated tool and checked by an experienced neuroradiologist on the T_2_-weighted image as the hyperintense regions around the tumour. The ROI will be propagated to the T_1_, T_2_, T_2_
^*^ and CBF maps. Voxel-wise and median values of R_1_, R_2_, R_2_
^*^ and CBF within the ROI will be calculated from the quantitative T_1_, T_2_, T_2_
^*^ and CBF maps, respectively. The reproducibility, repeatability and accuracy of the quantitative-MRI protocol will also be assessed using guidelines and a phantom developed by the National Institute of Standards and Technology and the International Society of Magnetic Resonance in Medicine (42).

On one hand, HTV will be defined via OE MRI as the proportion of voxels within the ROI being refractory in R_1_ for O_2_ challenge [i.e. ▵R_1_ ≤ 0, where ▵R_1_ = R_1_ (O_2_) – R_1_ (air)] and well-perfused (i.e. CBF > 0), as previously determined by experts in the field (36, 41, 43, 44). ▵R_1_ will be calculated in two ways. First, it will be calculated from the R_1_ maps obtained from the T_1_-mapping sequences acquired before [R_1_ (air)] and during O_2_ breathing [R_1_ (O_2_)]. Second, it will be calculated from T_1_ maps derived from the T_1_-weighted dynamic acquisition, such that R_1_ (air) is derived from the average of the first two R_1_ maps acquired at baseline while breathing air and R_1_ (O_2_) is derived from the last four R_1_ map acquired during oxygen breathing. ▵R_1_ values obtained with the two approaches will be compared. The approach which will provide the most reliable ▵R_1_ values in the test-retest scan across the entire patient cohort will then be selected to calculate the HTV. Voxel-wise ΔR_1_ values in the HTV will be converted into values of partial pressure of oxygen (pO_2_) using a similar approach to the one used by Chakhoyan et al. (35), which exploits known values of pO_2_ in normal appearing white and gray matter and uses these values to calibrate the pO_2_ values in the tumour. This approach will provide a way to quantitatively measure voxel-wise levels of hypoxia.

On the other hand, HTV will be defined via BOLD MRI by using a previously established method to estimate relative oxygen extraction fraction (rOEF) in human gliomas from T_2_, T_2_
^*^ and CBV maps (37). Briefly, the transverse relaxation due to local magnetic field inhomogeneities in a blood vessel network, 
$R_{2}^{'}$
, will be calculated within the ROI from T_2_ and T_2_
^*^ maps according to Equation 1:

(1)
$$R_{2}^{'}=R_{2}^{*}-R_{2}=\left(\frac{1}{T_{2}^{*}}-\frac{1}{T_{2}}\right)$$

Then, the Yablonskiy and Haacke model will be applied to derive the oxygen extraction fraction (OEF) according to Equation 2:

(2)
$$OEF=\frac{R_{2}^{'}}{\zeta \cdot \gamma \cdot \frac{4}{3}\cdot \pi \cdot \Delta \chi \cdot B_{0}}$$

where 
ζ
 is the venous fraction of the blood network and approximately equals the venous blood volume (~0.75.CBV), 
$B_{0}$
 is the magnetic field strength, 
γ
 is the gyromagnetic ratio of value 2.675 . 10^8^ s^-1^ T^-1^, 
△χ
 is the susceptibility difference between deoxygenated and oxygenated blood 
$△\chi =△\chi_{0}\cdot Hct=0.924\cdot 10^{-7}$
, which is calculated from the susceptibility difference between fully deoxygenated and fully oxygenated hemoglobin 
$△\chi_{0}=0.264\cdot 10^{-6}$
 and the small-vessel hematocrit (Hct = 0.35). As the absolute quantification of venous CBV in patients is not feasible, the venous blood vessel fraction 
ζ
 is approximated by CBV and the remaining factors are grouped into a constant 
$c=\gamma \cdot \frac{4}{3}\cdot \pi \cdot △\chi \cdot B_{0}=317\;s^{-1}$
. Using these simplifications, rOEF can be calculated according to Equation 3:

(3)
$$rOEF=\frac{R_{2}^{'}}{CBV\cdot c}=\left(\frac{1}{T_{2}^{*}}-\frac{1}{T_{2}}\right)\cdot \frac{1}{CBV\cdot c}$$

To derive the HTV, a hypoxia rOEF threshold (rOEF_hypoxia_) will be defined from the mean, rOEF_mean_, and the standard deviation, rOEF_SD_, of the tissue within the ROI, such that rOEF_hypoxia_ = rOEF_mean_ + rOEF_SD_. Finally, the HTV will be defined by all voxels within the ROI for which rOEF> rOEF_hypoxia_. Hypoxia levels in voxels belonging to the HTV will be measured by rOEF values.

To facilitate the assessment of spatial and quantitative voxel-wise correlations in HTV and in levels of tumour hypoxia defined by the different imaging biomarkers, all MRI images will be resampled into the spatial resolution of the MRI image with the highest resolution by linear interpolation of voxel-wise intensity values.

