## Introduction

1

Glioblastoma (GBM) is the most aggressive type of brain cancer and carries an extremely poor prognosis, which is reflected in 5-year survival of 5% and an overall median survival time of approximately 17 months following first-line treatment (1). After standard of care treatment, involving maximal safe resection of the bulk tumour mass followed by adjuvant chemoradiation treatment, most tumours recur locally, highlighting the failure of current treatment approaches to sustain local control (2, 3). The large intra- and inter-tumour heterogeneity characterising GBMs and the ability of GBM cells to dynamically adapt during the course of treatment and develop treatment resistance mechanisms are causes of local treatment failure (4). As such, the future of improved treatment outcomes for GBM patients relies on personalised treatment strategies targeting known mechanisms of treatment resistance.

Hypoxia, which is often present in subregions of GBM tumours, is the leading cause of resistance to radiotherapy, is predictive of the local sites of recurrence and is associated with poor clinical outcomes in GBM (5–12). Current standard of care treatment does not account for tumour hypoxia. The ability to image tumour hypoxia at various stages of treatment offers opportunities to personalise and improve treatments for GBM patients (13). For instance, preoperative imaging of tumour hypoxia offers the opportunity for supramarginal resections in surgical planning beyond current neurosurgical standard of care guidelines (14). Identifying hypoxic regions by using specialised imaging potentially allows adaptive radiotherapy treatment planning and delivery strategies to selectively dose escalate to radioresistant tumour regions, thus increasing the likelihood of local control (10, 15). Identifying hypoxic tumour regions harbouring progression at follow up is key to intervening at an early stage of tumour recurrence and personalising therapy tailored to the tumour response to treatment (16).

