### Study objectives

2.1

The study has one primary and four secondary objectives (**Figure 1**). The primary objective is to evaluate the spatial and quantitative correlations between OE and BOLD MRI measurements of hypoxia and [^18^F]MISO values of uptake in the tumour once before patients receive surgery and once prior to commencement of chemoradiation treatment. The secondary objectives are: 1) to evaluate the repeatability of the MRI biomarkers of hypoxia by means of test-retest scans acquired prior to patients commencement of chemoradiation treatment; 2) to develop a framework to integrate image-derived tumour hypoxia information into radiation treatment plans and estimate the potential clinical benefits of this approach compared to conventional radiation treatment; 3) to evaluate the ability of MRI biomarkers of hypoxia to assess tumour response to chemoradiation treatment; 4) to evaluate whether changes in the MRI biomarker of hypoxia observed during chemoradiation treatment are predictive of patient overall survival. Secondary objectives 3 and 4 of this study are exploratory.

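### The T2-hyperintensity ROI has no post-operative version and the BOLD hypoxic volume has no perfusion condition, so cavity or blood voxels can enter it at the second primary time point

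*Protocol article*

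**What the plan says.** **ROI.** Protocol article, section 2.7.2 (MRI analysis), has a single rule. The ROI is drawn with a semi-automated tool and "checked by an experienced neuroradiologist on the T_2_-weighted image as the hyperintense regions around the tumour". It is propagated to the T1, T2, T2* and CBF maps, and section 2.7.4 carries the same ROI to the PET image. No other ROI rule is given, and neither a resection cavity nor blood products are mentioned anywhere.

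**Time points.** Section 2.1 evaluates the primary correlations "once before patients receive surgery and once prior to commencement of chemoradiation treatment". Section 2.4 times the second scan as "prior to commencement of chemoradiation treatment (3-4 weeks post-operative". The Introduction describes the surgery in between as "maximal safe resection of the bulk tumour mass followed by adjuvant chemoradiation treatment".

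**The three HTV rules.**
- OE MRI (2.7.2): ROI voxels with ΔR1 ≤ 0 and CBF > 0.
- PET (2.7.4): ROI voxels with TBR ≥ 1.2 and CBF > 0.
- BOLD MRI (2.7.2): rOEF = (1/T2* − 1/T2)/(CBV·c), and "the HTV will be defined by all voxels within the ROI for which rOEF> rOEF_hypoxia". The threshold uses the mean and standard deviation "of the tissue within the ROI, such that rOEF_hypoxia_ = rOEF_mean_ + rOEF_SD". No perfusion condition is stated.

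**Criterion.** Section 2.3.1 calls Dice above 0.75 a good spatial correlation.

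**The concern.** The ROI rule is anchored on T2 brightness around a tumour. At the second primary scan most of that tumour may have been removed. Fluid in the cavity is T2-bright and so satisfies the rule as written, and blood at the margin may lie inside or beside the bright region.

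BOLD is the most exposed of the three measures, for three reasons:
- Blood products shorten T2* more than T2, which raises R2' without hypoxia.
- Low CBV sits in the denominator, so poorly perfused residue can also give a high rOEF.
- The cut-off comes from the same ROI. High outlying voxels enter the HTV and also raise the threshold, which pushes tumour voxels out.

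OE and PET at least require CBF > 0. That removes unperfused voxels but not perfused voxels that contain blood products.

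At stake is the BOLD comparison at one of the two primary time points. The test-retest scans of secondary objective 1 are also taken before chemoradiation. Residual blood that is stable between test and retest could favour BOLD repeatability for reasons unrelated to hypoxia. That is a direction only; its size was not calculated.

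**Working it through.** **1. The plan's own figures.** With the section 2.7.2 inputs and the stated 3 T field, c = 2.675·10⁸ × 4/3 × π × 0.924·10⁻⁷ × 3 = 310.6 s⁻¹, against the stated 317 (2% apart). This does not matter here: a constant multiplies every rOEF value and the mean + SD threshold alike, so it cancels. No sample size figure is involved. The article gives no residue fraction, R2' or CBV value, so everything below is an illustration on assumed inputs.

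**2. Direction, from the formula.** rOEF is proportional to R2'/CBV. For residue relative to ordinary ROI tissue:
- R2' ×4, CBV unchanged (blood-like): rOEF ×4.
- R2' ×0.5, CBV ×0.1 (poorly perfused): rOEF ×5.
- R2' ×0.1, CBV ×0.1 (fluid in which both fall together): rOEF ×1, so no enrichment.

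**3. One case worked by hand.** Assumptions: voxel rOEF lognormal with log-SD 0.25; 20% of non-blood voxels hypoxic at 1.6 times normal; blood multiplies rOEF by 3. Ordinary voxels have mean e^0.03125 = 1.0317 and mean square e^0.125 = 1.1331.

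Clean ROI:
- Mean = 1.0317 × (0.8 + 0.2×1.6) = 1.1556.
- Mean square = 1.1331 × (0.8 + 0.2×2.56) = 1.4867.
- SD = √(1.4867 − 1.3353) = 0.389, so the threshold is 1.545.
- Hypoxic voxels above it: 55.6%. Normal voxels above it: 4.1%.
- HTV = 0.1112 + 0.0327 = 0.1439. Dice = 2×0.1112/(0.1439 + 0.20) = 0.65.

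Blood in 5% of the ROI:
- Mean = 1.0317 × (0.95×1.12 + 0.05×3) = 1.2525.
- Mean square = 1.1331 × (0.95×1.312 + 0.05×9) = 1.9222.
- SD = 0.594, so the threshold is 1.847.
- Hypoxic voxels above it: 28.3%. Normal: 0.7%. Blood: 97.4%.
- HTV = 0.0538 + 0.0054 + 0.0487 = 0.1079. The blood share is 0.0487/0.1079 = 45%. Dice = 2×0.0538/(0.1079 + 0.19) = 0.36.

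Both effects are visible: blood supplies almost half of the HTV, and the raised cut-off halves the share of hypoxic voxels detected.

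**4. Range under the same model (simulation).** Dice of the BOLD HTV with the truly hypoxic voxels:

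| Blood in ROI | R2' factor | Hypoxic rOEF 1.6× | Hypoxic rOEF 2.5× |
|---|---|---|---|
| none | – | 0.65 | 0.87 |
| 1% | 3 | 0.59 | 0.83 |
| 5% | 1.5 | 0.59 | 0.86 |
| 5% | 2 | 0.52 | 0.80 |
| 5% | 3 | 0.36 | 0.70 |
| 10% | 3 | 0.18 | 0.55 |

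Runs differ by about 0.01.

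**5. A second model, varying R2' and CBV separately.** R2' and CBV are lognormal, log-SD 0.35 each. Dice is against the HTV that the same rule gives on the clean tissue alone. Residue is 5% / 10% / 20% of the ROI.

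| Residue | Share of BOLD HTV | Dice |
|---|---|---|
| R2' ×4, CBV ×1 | 53% / 83% / 97% | 0.36 / 0.15 / 0.03 |
| R2' ×0.5, CBV ×0.1 | 66% / 92% / 99% | 0.24 / 0.07 / 0.01 |
| R2' ×0.1, CBV ×0.1 | 5% / 10% / 20% | 0.97 / 0.95 / 0.89 |

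The effect therefore runs from negligible to dominant, depending on how much residue enters the ROI and on its R2'/CBV ratio.

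**The case against.** The strongest reply is that the article does not say the ROI takes in all T2-bright tissue. It speaks of hyperintense regions around the tumour, checked by an experienced neuroradiologist who could leave the cavity out. Blood products are not uniformly T2-bright, so some would fall outside the ROI anyway. Contouring detail may also sit in a full protocol or imaging manual that is not shown. All of this stands against a stronger reading that a reader might infer, namely that the plan includes surgical residue and that BOLD will label it hypoxic. The documents do not support that certainty. The reply does not remove the point. The criterion written down is T2 brightness, which cavity fluid meets, and section 2.7.2 is otherwise specific enough to give equations and thresholds. The missing BOLD perfusion condition is a difference between stated rules, not an omitted detail.

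Second, the size rests on chosen inputs. This is correct. With 1% blood, or a 1.5-fold R2' factor, the loss is small. In the 1.6-fold column Dice is 0.65 with no blood at all, already below 0.75. A BOLD-PET mismatch after surgery could therefore not be put down to surgery alone.

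Third, two wider consequences do not follow from the text. Section 2.3.5 names no baseline for HTV change, and objective 4 is labelled exploratory. Only the OE HTV is defined as a proportion of the ROI, so a diluted denominator does not affect the primary Dice.

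**Conclusion.** The point holds as a risk that nothing in the stated rules prevents. One ROI rule serves scans before and after resection, and BOLD alone lacks the CBF > 0 condition while dividing by CBV and setting its threshold within the ROI. Cavity or blood voxels can therefore enter the BOLD HTV at the second primary time point and displace tumour voxels.

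The size cannot be fixed from the documents. Under the assumed inputs, contamination can take a marker that would pass the 0.75 criterion (0.87) below it (0.70 with 5% blood at 3-fold R2', about 0.55 with 10%). With 1% blood it would still pass (0.83). Fluid whose R2' and CBV fall together does little harm. The figures assume the lognormal spread, the 20% hypoxic share, the hypoxia contrast and the residue factors; none is a trial value.

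The point merits a correction to section 2.7.2. It does not show that the post-operative BOLD results will be invalid.

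**What to change.** In section 2.7.2:

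1. Define the ROI at post-operative time points as T2-hyperintense tissue minus the resection cavity and minus blood products, as identified by the neuroradiologist on the pre-contrast T1 (MP2RAGE) and T2 images. Do not use a T2* threshold: T2* enters R2', so a short-T2* cut could remove the high-rOEF voxels that BOLD is meant to detect.
2. Fix this mask before PET or HTV maps are viewed. Use the same ROI for OE, BOLD and PET, and the same rule for test and retest.
3. Apply CBF > 0 to the BOLD HTV as for OE and PET, and compute rOEF_mean and rOEF_SD over those voxels only. The perfusion condition does not replace the mask, because perfused voxels containing blood products would pass it.
4. Report Dice and correlation separately for the pre-operative and post-operative scans. The article does not say that they will be pooled; stating the separation lets a reader see whether agreement changes after surgery.

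The cost is a little more contouring by the same reader on images already acquired, a few sentences of text, and smaller post-operative ROIs. No extra scans are needed. If an imaging manual already contains these exclusions, a reference to it would meet items 1 and 2.
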